### Randomization

Randomization will be performed after the eligibility assessment and baseline assessment. The Department of Science and Technology of SUTCM will generate the randomization sequence using a random number generator (IBM, Chicago, IL, USA) and then placed in a sequenced, sealed, opaque envelope. When potential participants meet the inclusion criteria, the envelope can be opened and the subject will accept the corresponding measures. Then, eligible patients will be randomly divided into a guideline therapy group and a guideline therapy plus TCMR group, with an allocation proportion of 1:1.

### Blinding

Participants and therapists are unable to be blinded regarding group assignments due to the specific intervention, but the therapists will be masked to the evaluation of outcomes. To reduce the risk of bias, the outcome assessors, data managers, and statisticians will be unaware of the group assignments during the outcome evaluation and data analysis process. They will be required not to share study information. The blinding procedure will be in place until the data are locked.

### Data collecting and monitoring

The administrators at the Science and Technology Department of SUTCM will be responsible for monitoring data management as an independent third party. Paper case report forms (CRFs) will be designed to collect test data according to the trial protocol, which will be stored in a securely locked location. We will conduct a double independent data entry to promote data quality. Then, it will be locked and analyzed by an independent statistician under the supervision of the administrators. The test data will be recorded on the sub-website of China Clinical Trial Center (http://www.medresman.org.cn/login.aspx) electronic data management system. The electronic database will be closed after data entry is completed. The administrators report the data supervision to the steering committee every week, mainly including the reliability of the data and the accuracy of the entry.

### Statistical analysis

#### General analysis principles

Statistical analysis will be performed using IBM SPSS version 25.0 (IBM Corp., Armonk, NY, USA). A Kolmogorov-Smirnov test with Lilliefors correction will be used to analyze all quantitative variables to determine whether they follow a normal distribution. Nonnormally distributed data will be expressed as the median (upper and lower quartiles), and normally distributed data will be expressed as the mean ± the standard deviation (SD). Categorical variables will be presented as frequencies and percentages. The level of significance will be *α* < 0.05 with a two-tailed test, and 95% confidence intervals will be presented where appropriate.

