### Primary outcome measurements

#### Modified Medical Research Council (mMRC) Dyspnea Scale

We will use the mMRC as the primary outcome indicator to evaluate the dyspnea symptoms and physical health; this scale is a good indicator of the functional capacity of patients’ lungs [22]. Evaluation of the outcomes will occur at three points (before treatment, the 7th day during hospitalization, and the discharge day). The mMRC [22, 23] grades are as follows: mMRC grade 0, dyspnea occurs only during strenuous exercise; mMRC grade 1—the patient has shortness of breath when walking on flat ground or walking on a small slope; mMRC grade 2—due to shortness of breath, when walking on flat ground, the patient is slower than another person of the same age or needs to stop to rest; mMRC grade 3—when walking on flat ground for approximately 100 m or after a few minutes, the patient needs to stop to pant; and mMRC grade 4—due to severe breathing difficulties, the patient cannot leave the house or has breathing difficulties when dressing or undressing. We will assess the mMRC with a repeated longitudinal analysis.

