### Sample size calculation

The PASS software (PASS 11, NCSS, LLC, Kaysville, UT, USA) will be used to estimate the sample size utilizing two independent sample means (*α* = 0.05, *β* = 0.10). We will use the mMRC as the primary efficacy outcome. Based on previous clinical studies on the effect of respiratory symptoms after acupressure therapy plus Liu Zi Jue Qigong interventions, the mMRC Scale score in the control group is 0.52 with a standard deviation of 0.11 [27], and the average mMRC Scale score in the treatment group is 0.95 with a standard deviation of 0.92. In this study, the target sample size will be 64 participants in each group, anticipating on maximum loss to follow-up of 20%.

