#### Analysis of primary outcome

The primary outcomes will be evaluated at baseline, 6 days after the intervention, and upon discharge based on the intention-to-treat analysis (ITT). The primary endpoint of the trial is the mean change in mMRC Scales from baseline to the discharge day. Baseline covariates included for adjustment were sex, age category, history of cardiopulmonary disease, and body weight category. The whole outcomes scale was also measured at baseline. When the data have a normal distribution, two-way repeated-measures ANOVA will be used as the main analytic method, and a paired sample *t* test will be used between the two intervention groups; if the normal distribution is not met, the Wilcoxon test will be used as an alternative method. Prior to any analysis, any missing data pattern will be investigated and reasons for missing data obtained and summarized where possible. The percentage of missing data is 20%, and we plan to generate 5 imputed datasets, which is the minimum recommended number [28]. The sensitivity analyses were carried out to assess two assumptions about missing data, and data imputation scenarios can potentially influence the primary result [29]. To account for missing data, our primary analyses were conducted on an imputed data set where missing values were generated using multiple imputation by chained equations (MICE) [30].

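### The endpoint and sample size rest on the mean change in mMRC, but the normality rule, followed literally, will almost certainly replace that estimate with medians and a rank test

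*Protocol article*

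**What the plan says.** The protocol article, under Analysis of primary outcome, fixes the target: "The primary endpoint of the trial is the mean change in mMRC Scales from baseline to the discharge day". The Sample size calculation works on the same scale, "utilizing two independent sample means (*α* = 0.05, *β* = 0.10"), with means of 0.52 and 0.95.

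General analysis principles sets the reporting rule. The trigger is "A Kolmogorov-Smirnov test with Lilliefors correction will be used to analyze all quantitative variables to determine whether they follow a normal distribution". The consequence is "Nonnormally distributed data will be expressed as the median (upper and lower quartiles"); the mean with its SD is kept for variables that pass. Analysis of primary outcome attaches a change of test to the same trigger: "if the normal distribution is not met, the Wilcoxon test will be used as an alternative method".

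The only general statement about estimates is "The level of significance will be *α* < 0.05 with a two-tailed test, and 95% confidence intervals will be presented where appropriate", which does not say what the interval is for. Analysis of secondary outcomes says that a difference between arms will be estimated and tested for each secondary endpoint, in a way similar to the primary analysis, but does not name the measure of difference either.

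**The concern.** The endpoint and the sample size are stated in means. The reporting rule keeps the mean only for data that pass a normality test, and the fallback test does not estimate a mean change. If the primary variable can hardly ever pass, the fallback becomes the plan in practice, and the article does not say that the quantity the trial was sized for will still be estimated.

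The mMRC has five whole grades, starting at "mMRC grade 0, dyspnea occurs only during strenuous exercise" and ending at grade 4, so each patient's change is a whole number from -4 to +4. The median of such data is a whole number, or a half when the number of patients is even and the two middle values differ. A planned effect of 0.43 grade is finer than that. At stake is whether readers see the size of the effect, with its uncertainty, or a p-value beside medians that either tie or jump by a full grade. This is a matter of what is estimated and shown. Changing the test alone would leave the median rule in force.

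**Working it through.** **1. The plan's own sample size.** Inputs from Sample size calculation: difference 0.95 - 0.52 = 0.43, SDs 0.11 and 0.92, α = 0.05, power 0.90, 20% loss. Two-sided testing comes from General analysis principles.

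- Normal approximation: n = (1.960 + 1.282)² × (0.11² + 0.92²) / 0.43² = 10.51 × 0.8585 / 0.1849 = 48.8, so 49 per arm, and 49/0.8 = 61.3, so 62.
- Unequal-variance t test: 51 per arm, and 51/0.8 = 63.75, so 64. This matches the stated 64.

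The trial is therefore sized on a two-sided comparison of means, with 64 × 0.8 ≈ 51 completers per arm if the full loss occurs.

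**2. Does the rule trigger?** The article gives no distribution for the change score, so one is assumed: normal values rounded to whole grades and limited to -4 to +4. The stated control SD of 0.11 cannot be used, because whole-grade values with mean 0.52 have an SD of at least √(0.52 × 0.48) = 0.50. A common SD is used instead: 0.92 as the main case, 0.66 to 1.2 as the range. The two stated means are treated as amounts of improvement, although the article calls them scores.

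- SD 0.66 to 1.2, n = 51 or 64: Lilliefors rejects at 0.05 in 100% of the simulated arms tested.
- SD 1.6: rejects in 96.0% (n = 51) to 99.6% (n = 64).
- SD 2.0: rejects in 84% to 91%.

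**3. What does the prescribed summary show?** True difference 0.43, SD 0.92, 64 per arm, 8,000 simulated trials per row:

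| Assumed control mean | TCMR mean | Arm medians identical | Median and both quartiles identical |
|---|---|---|---|
| 0.30 | 0.73 | 10% | about 8% |
| 0.52 | 0.95 | 51% | about 14% |
| 0.70 | 1.13 | 89% | about 6% |
| 0.90 | 1.33 | about 85% | 6% to 7% |

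The pattern follows the rounding. Means of 0.70 and 1.13 both round to 1, so the medians tie. Means of 0.30 and 0.73 fall on either side of 0.5, so the medians mostly differ by a whole grade, which overstates 0.43. A control mean of 0.52 sits at the boundary. Over SDs of 0.66 to 1.2, control means of 0.52 to 1.5 and n of 51 or 64, identical medians range from 3% to 99%, and an identical full summary from 0.2% to 37%.

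At control mean 0.52 and SD 0.92, the Wilcoxon test is still significant in 40% (n = 51) to about half (n = 64) of the trials whose medians tie.

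**4. A constructed example, 64 per arm.** Control changes of 0/1/2/3 grades in 16/32/12/4 patients; TCMR in 6/32/18/8.

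- Control mean: (32 + 24 + 12)/64 = 1.06. TCMR mean: (32 + 36 + 24)/64 = 1.44. Difference: 24/64 = 0.375.
- Both SDs are 0.833, so SE = 0.833 × √(2/64) = 0.147, and the 95% CI is about 0.08 to 0.67.
- Both medians are 1. Quartiles are 0.75 and 1.25 against 1 and 2. Wilcoxon p = 0.011. Both arms fail Lilliefors (p about 0.001).

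The rule would print 1 against 1 with p = 0.011. The quartiles hint at a shift, but neither its size on the planned scale nor its precision appears.

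**5. What the mean difference would give.** With the plan's root-mean-square SD √(0.8585/2) = 0.655 and 51 per arm, the 95% CI half-width is about 1.96 × 0.655 × √(2/51) = 0.25. With the assumed SD of 0.92 it is 1.96 × 0.92 × √(2/51) = 0.36. Either is informative against 0.43.

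**The case against.** Four points can fairly be made for the plan.

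- **The rule shows quartiles as well as the median.** This stands. When medians tie at control means of 0.52 to 0.9, a quartile differs in roughly 73% to 94% of trials. A reader might infer that a benefit of planned size would usually look like no difference at all. Nothing supports that: the complete printed summary is identical in only a minority of trials, and a Wilcoxon p-value is still given.
- **A general display convention need not override a specific endpoint definition.** This stands in part. Nothing forbids reporting the mean as well, and the text on secondary outcomes shows that estimating a difference is intended. A reader might conclude that the endpoint will go unreported; the article does not say so. What it does say is that the mean is kept for normal data, and it makes no exception for the primary endpoint.
- **Reporting layout belongs in the analysis plan.** This would answer a mere omission. Here the article states a rule that conflicts with its own endpoint, so the conflict needs resolving where it is stated.
- **The size depends on assumptions.** This stands. The article gives no distribution of change scores, and the rate of tied medians moves across almost the whole range with the control mean and SD.

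Reading mMRC as categorical, with frequencies and percentages, would avoid the median rule, but it would still not report a mean change, and the article itself treats the scale as a mean.

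**Conclusion.** The inconsistency is real and should be corrected. Endpoint and sample size are on the mean scale. The branch that will almost certainly apply reports medians with quartiles and a rank p-value, without committing to the mean difference.

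Failure of the normality test is a practical near-certainty for spreads of 0.66 to 1.2 at 51 to 64 per arm. It is not a logical necessity, and it weakens at implausibly wide spreads. The visible consequence is uneven. At an assumed SD of 0.92 and 64 per arm, medians tie in about 10% to 90% of trials (about 51% at the article's control mean of 0.52), while the full summary ties in about 6% to 14%. These rates rest on the rounded-normal model and on reading the two planning means as improvements. The mismatch between endpoint and reporting rule depends on neither.

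**What to change.** Under Analysis of primary outcome, state that, whatever the normality result, mMRC change from baseline to discharge is reported as mean (SD) per arm and as the between-arm mean difference (TCMR minus control) with 95% CI. Take the estimate and the primary p-value from one named model, so that the interval and the test cannot disagree. One candidate is a linear model of change on arm, baseline mMRC and the covariates already listed in that section, pooled over the imputed datasets. Add the number of patients in each grade per arm.

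Medians and quartiles may be shown alongside. The rule under General analysis principles can stay for other variables; removing medians from PHQ-9, Barthel and symptom scores, where skew is plausible, is not needed.

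The cost is small: a short addition to the text, one more estimate to tabulate and no new data. The Wilcoxon test becomes supportive for the primary endpoint, as does the repeated-measures ANOVA if the named model is a different one.

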#### Analysis of primary outcome

The primary outcomes will be evaluated at baseline, 6 days after the intervention, and upon discharge based on the intention-to-treat analysis (ITT). The primary endpoint of the trial is the mean change in mMRC Scales from baseline to the discharge day. Baseline covariates included for adjustment were sex, age category, history of cardiopulmonary disease, and body weight category. The whole outcomes scale was also measured at baseline. When the data have a normal distribution, two-way repeated-measures ANOVA will be used as the main analytic method, and a paired sample *t* test will be used between the two intervention groups; if the normal distribution is not met, the Wilcoxon test will be used as an alternative method. Prior to any analysis, any missing data pattern will be investigated and reasons for missing data obtained and summarized where possible. The percentage of missing data is 20%, and we plan to generate 5 imputed datasets, which is the minimum recommended number [28]. The sensitivity analyses were carried out to assess two assumptions about missing data, and data imputation scenarios can potentially influence the primary result [29]. To account for missing data, our primary analyses were conducted on an imputed data set where missing values were generated using multiple imputation by chained equations (MICE) [30].

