### Dropout and suspension criteria

During the intervention period, patients will have the right to withdraw for whatever reason and at whatever time under the protection of the Declaration of Helsinki [16]. In addition, if the hospitalization time is less than 7 days, the subject will be excluded as the outcome evaluation cannot be completed.

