### Interventions

For the emergency event of COVID-19, standard therapy has been developed in strict accordance with the National Diagnostic and Treatment Protocol (the 7th trial version). For patients, standard therapy is necessary to prevent death and other adverse consequences. On the basis of the guideline therapy, the test group will require a standardized TCMR program consisting of acupressure therapy and Liu Zi Jue Qigong exercises. The program will be performed twice a day at 10 am and 4 pm. Each time, acupressure will be performed first, and then Liu Zi Jue Qigong exercises will continue. Each treatment will last 20 min; thus, a total of 40 min will be needed. The TCMR program will be ongoing during the patient’s stay until the patient is discharged. There will be consensus in advance regarding the acupuncture points, pressure levels, and duration. Liu Zi Jue Qigong exercises will be demonstrated live by the therapists on the first day until the patient is able to perform the exercises skillfully. Patients will be provided with paper and video versions of the exercises to facilitate subsequent practice. Therapists performing rehabilitation therapy will be required to have 10 years of clinical experience in acupressure and Qigong therapy and have undergone rigorous clinical trial training before conducting trials until passing an exam to perform the intervention. Furthermore, both groups of the participants will be allowed to participate in normal exercise under the intervention conditions.

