### Outcome measurements

All outcomes will be managed by researchers masked to the group assignment; the outcomes will include the Modified Medical Research Council Dyspnea Scale, Activities of Daily Living Barthel Index Scale, Patient Health Questionnaire-9 Scale [21], and Respiratory Symptoms Scale. Evaluation of the outcomes will occur at three points (before treatment, the 7th day during hospitalization, and the discharge day).

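### The primary endpoint is read on the discharge day, a patient-specific time that may depend on recovery and on unblinded care, so a true benefit on the mMRC is likely to be attenuated

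*Protocol article*

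**What the plan says.** Analysis of primary outcome fixes the endpoint: "The primary endpoint of the trial is the mean change in mMRC Scales from baseline to the discharge day". It gives two-way repeated-measures ANOVA as the main method, with a Wilcoxon test as the alternative.

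Outcome measurements gives the assessment times: "Evaluation of the outcomes will occur at three points (before treatment, the 7th day during hospitalization, and the discharge day". Analysis of primary outcome words the middle visit differently: the outcome is "evaluated at baseline, 6 days after the intervention, and upon discharge based on the intention-to-treat analysis (ITT".

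Interventions ties exposure to the same event: "The TCMR program will be ongoing during the patient’s stay until the patient is discharged". Dropout and suspension criteria adds that "if the hospitalization time is less than 7 days, the subject will be excluded as the outcome evaluation cannot be completed".

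Blinding states: "Participants and therapists are unable to be blinded regarding group assignments due to the specific intervention". Outcome assessors, data managers and statisticians are masked. Under Adherence, nurses prompt patients to exercise, so at least some ward staff know who is in the TCMR arm. The article does not say what criterion governs discharge or who decides it. Length of stay is not among the outcomes, and nothing adjusts for it.

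**The concern.** The discharge day occurs after randomisation, and treatment may change when it comes. Three consequences follow.

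- If patients go home once their breathing has improved enough, both arms are read at a similar clinical state. Faster recovery under TCMR would then show mainly as a shorter stay, which the trial does not count as an outcome.
- Exposure and follow-up differ between patients and possibly between arms, yet the ANOVA treats discharge as one common occasion.
- Care is open-label and no masking of the discharge decision is described, so the time of measurement could differ by arm for reasons other than recovery.

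The exclusion of stays under 7 days adds to this. It acts after randomisation, would remove the fastest recoverers, and conflicts with the stated intention-to-treat basis.

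At stake is the meaning of the primary result. A small or null difference at discharge could hide a real benefit, and a difference of either sign could partly reflect when patients were sent home.

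**Working it through.** **1. Reproduce the planned sample size.** Inputs from Sample size calculation: means 0.52 and 0.95 (absolute difference 0.43), SDs 0.11 and 0.92, α = 0.05, power 90%, loss 20%. General analysis principles makes the test two-sided.

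Root-mean-square SD = √[(0.11² + 0.92²)/2] = √(0.8585/2) = 0.655.

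- Normal approximation: 49 per arm; 49/0.8 = 61.25, so 62.
- Equal-variance t test: 50 per arm; 50/0.8 = 62.5, so 63.
- Welch t test: 51 per arm (power 0.902); 51/0.8 = 63.75, so 64.

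The stated 64 per group is reproduced, so this point does not depend on a sample-size error.

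**2. Power if only part of the planned difference is visible at discharge.** With 51 evaluable per arm, SE = √(0.8585/51) = 0.1297, and power ≈ Φ(Δ/SE − 1.96).

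| Share of 0.43 retained | Δ | Δ/SE | Power |
|---|---|---|---|
| 100% | 0.430 | 3.31 | 91% |
| 75% | 0.3225 | 2.49 | 70% |
| 50% | 0.215 | 1.66 | 38% |
| 25% | 0.1075 | 0.83 | 13% |

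**3. How much might be lost: an illustrative simulation.** Every input is assumed. Latent dyspnoea starts at mean 3.0 (SD 0.6) and falls linearly, at a median of 0.13 grade per day in the control arm and 35% faster under TCMR. Observed grades carry error (SD 0.6) and are rounded to 0–4. Discharge time mixes a symptom-driven time (latent dyspnoea reaching 0.7) with an unrelated time (median 16 days). The link weight runs from 0 (unrelated) to 1 (fully symptom-driven). Stays are bounded at 7 to 60 days, with 400,000 patients per arm. Differences are TCMR minus control in mMRC change.

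| Link | Discharge day | Day 7 | Median stay, control / TCMR (days) |
|---|---|---|---|
| 0 | −0.336 | −0.323 | 16.0 / 16.0 |
| 0.25 | −0.291 | −0.322 | 16.3 / 15.1 |
| 0.5 | −0.235 | −0.325 | 16.6 / 14.3 |
| 0.75 | −0.145 | −0.321 | 17.0 / 13.5 |
| 1 | −0.020 | −0.323 | 17.3 / 12.8 |

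At link 0 the discharge reading shows slightly more than day 7. The loss relative to day 7 is 1 − 0.235/0.325 = 28% at half link, 1 − 0.145/0.321 = 55% at link 0.75, and 1 − 0.020/0.323 = 94% at full link.

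**4. Sensitivity to the model.** A one-grade-per-step recovery model was also tried. It assumed baseline grades 2/3/4 at 55/35/10% and discharge after two days at grade 1 or less. Under full linkage the discharge and day-7 differences were −0.08 vs −0.29, −0.10 vs −0.36 and −0.16 vs −0.54, a loss of about 70%. The loss was about 40–45% at half linkage and 10–20% with none. The direction is the same in both models; the size is not.

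**5. Limits.** Because stays are bounded below at 7 days, the simulation in step 3 does not show the effect of the early-stay exclusion. Its outcome SD is about 1.0, against the plan's 0.655. At 51 per arm its day-7 contrast has only about 38% power, so it does not show that day 7 is adequately powered. It shows only how discharge timing can absorb an effect.

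**The case against.** The strongest reply is that the article nowhere says patients leave when their dyspnoea has resolved. Without a stated criterion, saying that the arms are compared when equally well is an inference. If discharge is governed by something else, little is lost. This stands, and it is why the size must be given as a range.

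A reader might infer that about 90% of the effect disappears and that the endpoint is biased toward no difference by design. The documents do not support this. A loss that large needs discharge to be fully tied to dyspnoea, and even then it depends on the model (94% in one, about 70% in the other). If unblinded staff timed discharge differently by arm, the bias could also run the other way.

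A reader might also infer that the trial cannot compare dyspnoea at a common time. It can: the day-7 mMRC is collected and sits inside the repeated-measures model. What stands is that this contrast has no primary status, because the named endpoint is the discharge-day change.

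Finally, status at the end of treatment is a coherent question. It is easier to interpret when treatment length is fixed; here that length ends with an event that may itself follow recovery.

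**Conclusion.** The point holds in a bounded form. The primary endpoint is measured at a patient-specific, post-randomisation time, so a difference at discharge cannot be separated from discharge timing. That follows from the article's own text and needs no simulation.

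Attenuation is the likely direction if discharge follows dyspnoea relief. Background calls dyspnoea the most obvious symptom, which makes some link plausible, but the strength of the link is unknown. Under the assumed models the loss relative to day 7 ranges from none or 10–20% (no link) to about 70–94% (full link). On the plan's own difference and SDs, retaining half of the 0.43 cuts power from about 91% to about 38%.

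This should be corrected, with moderate confidence in its practical size. It does not show that the trial will miss a benefit.

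**What to change.** - **Primary contrast.** Name the change in mMRC from baseline to the already scheduled day-7 assessment. Reconcile the two wordings of that visit. The Abstract has TCMR running from admission, so hospital day 7 and six days after treatment starts coincide if the first treatment day is day 1. State the anchor explicitly.
- **Stays under 7 days.** Do not exclude these patients from the primary intention-to-treat analysis. Use their discharge grade or the planned multiple imputation, and test that choice in a sensitivity analysis. The discharge grade is itself a recovery-timed reading, so neither option is neutral.
- **Discharge-day change.** Keep it as secondary, reported beside time to discharge by arm. Recording of the discharge date is implied by the discharge-day visit; confirm it.
- **Sample size.** State that the 0.43 difference was not derived for day 7.
- **Timing.** Make the change before data lock and before the statisticians are unblinded, with a dated registry update. Quality control allows a change of primary outcome with steering and ethics committee authority.

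**Cost.** A protocol amendment and registry update are needed, but no new visit for patients still in hospital. The primary reading would cover only about one week of TCMR. Recruitment was expected to end on 30 June 2020 and this version is dated 8 July 2020, so the change is late, in a trial whose participants and therapists are unblinded. It must be openly disclosed with its reason.

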### Exclusion criteria

Those who meet one of the following conditions will be removed: (1) patients with complications of other serious underlying diseases, such as chronic obstructive pulmonary disease, obstructive pulmonary disease, coronary heart disease, and hypertension; (2) patients with serious mental illness; (3) patients with cognitive dysfunction who are unable to understand the trial process and rehabilitation content; (4) patients with severe bone and joint diseases (such as spinal arthritis, severe osteoporosis, and periarthritis) affecting limb function and movement; (4) patients with respiratory failure who require mechanical ventilation or patients with shock or combined organ failure requiring intensive care unit (ICU) monitoring and treatment; (5) pregnant or lactating women; and (6) patients who participate in other forms of exercise during the trial.

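### The adjustment list does not name baseline mMRC, includes a history covariate that the exclusion criteria largely empty, and would be lost under the Wilcoxon fallback

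*Protocol article*

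**What the plan says.** Under Analysis of primary outcome the endpoint is a change score: "The primary endpoint of the trial is the mean change in mMRC Scales from baseline to the discharge day". The covariates follow: "Baseline covariates included for adjustment were sex, age category, history of cardiopulmonary disease, and body weight category". The next sentence reads "The whole outcomes scale was also measured at baseline" and does not say whether those baseline values are covariates.

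The same section names the tests. Under normality, "two-way repeated-measures ANOVA will be used as the main analytic method", together with a paired t test for comparing the groups. Otherwise, "if the normal distribution is not met, the Wilcoxon test will be used as an alternative method". Under Analysis of secondary outcomes, a similar approach applies to the other scales.

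Two other sections bear on this:

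- Exclusion criteria, item (1), removes "patients with complications of other serious underlying diseases, such as chronic obstructive pulmonary disease, obstructive pulmonary disease, coronary heart disease, and hypertension".
- Randomization places allocation after the baseline assessment, so a baseline mMRC should exist for every randomised patient. The section describes no stratification.

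**The concern.** Three features of the plan work against each other.

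- **Baseline score.** The variable most directly tied to the outcome, the patient's own starting mMRC, is not in the list. Subtracting it is not the same as adjusting for it, because subtraction fixes the slope of discharge on baseline at 1. If the true slope is lower, the change score is noisier than it need be and pushes a chance baseline difference too far the other way.
- **History covariate.** One of the four listed covariates records diagnoses that the exclusion criteria are written to keep out.
- **Tests.** The paired t test and the Wilcoxon test have no place for covariates, so whether the primary result is adjusted at all depends on the outcome of a normality test.

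At stake are precision and protection against chance imbalance. The comparison remains unbiased over repeated randomisation either way.

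**Working it through.** **1. The plan's own sample size.** Inputs from Sample size calculation: means 0.52 and 0.95, SDs 0.11 and 0.92, alpha 0.05, power 0.90, 20% loss. General analysis principles makes the test two-sided.

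- Difference: 0.95 − 0.52 = 0.43.
- Root-mean-square SD: √((0.11² + 0.92²)/2) = √0.42925 = 0.655.
- Per group, before and after dividing by 0.8: normal formula 49, then 62; equal-variance t test 50, then 63; Welch t test 51, then 64.

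The stated 64 per group is reproduced exactly by the Welch calculation. It uses no covariates. After 20% loss, 64 × 0.8 = 51.2, or about 51 per arm. Power there is Φ(0.43/(0.655 × √(2/51)) − 1.96) = Φ(3.31 − 1.96) ≈ 0.91.

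**2. Change score against ANCOVA.** Let baseline and discharge both have variance σ² and correlation ρ.

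- Change score: 2σ²(1 − ρ).
- ANCOVA residual: σ²(1 − ρ²).
- Ratio ANCOVA/change: (1 − ρ²)/(2(1 − ρ)) = (1 + ρ)/2.

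The article gives no ρ, so a range of 0.3 to 0.7 is assumed. It also does not say whether the planning SDs describe scores or changes, so both readings are shown, at 51 per arm and a difference of 0.43.

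| ρ | Variance ratio | Reduction | Power if 0.655 is the SD of change: change → ANCOVA | Power if 0.655 is the SD of the discharge score: change → ANCOVA |
|---|---|---|---|---|
| 0.3 | 0.65 | 35% | 0.91 → 0.98 | 0.80 → 0.94 |
| 0.5 | 0.75 | 25% | 0.91 → 0.97 | 0.91 → 0.97 |
| 0.7 | 0.85 | 15% | 0.91 → 0.95 | 0.99 → 1.00 |

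With unequal variances the size of the gain changes but not its direction. Change variance minus ANCOVA variance is σx² + σy² − 2ρσxσy − σy²(1 − ρ²) = (σx − ρσy)², which is never negative.

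**3. Chance imbalance.** With equal variances the true slope is ρ. If the arms differ at baseline by D, the change comparison is shifted by (ρ − 1)D: an over-correction of 70%, 50% or 30% of D at ρ = 0.3, 0.5 or 0.7. ANCOVA with the fitted slope removes this in expectation.

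**4. The history covariate.** For a binary covariate with prevalence p and effect d in SD units, R² ≈ p(1 − p)d²/(1 + p(1 − p)d²). Prevalence and effect are assumptions.

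- p = 0.02, d = 0.3: 0.00176/1.00176 ≈ 0.2%.
- p = 0.10, d = 0.8: 0.0576/1.0576 ≈ 5%.

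**5. The fallback.** The mMRC has five grades (0 to 4), so the data are heavily tied. General analysis principles applies a Kolmogorov-Smirnov test with Lilliefors correction to all quantitative variables. Such a scale is unlikely to pass as normal, so the Wilcoxon route, which carries no covariates, may well become the primary analysis.

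**The case against.** Much of the opposing case stands, and it limits the point.

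- **Baseline is not unused.** A reader might infer that the plan ignores the strongest predictor. It does not: baseline enters by subtraction and as a repeated-measures occasion. Nor does any figure in the article show that baseline mMRC is the strongest predictor.
- **The sentence after the list may be meant to add the baseline scores.** That is possible, but it says only that they were measured. If they are meant as covariates, the text should say so.
- **The history covariate is not necessarily constant.** The exclusion concerns serious disease and gives examples. Mild, resolved or unlisted conditions could remain, so little variation is expected, but zero variation is not shown.
- **The main method can adjust.** A reader might infer that none of the named methods can take covariates. Repeated-measures ANOVA can, and the four listed variables could enter as between-subject terms. The limit applies to the paired t test and the Wilcoxon fallback only. Leaving the model's detail to an analysis plan would be normal, but naming tests that cannot carry the stated adjustment is a conflict within the article.
- **A power shortfall does not follow.** Setting the SD at 0.92 in both arms would give about 65% power for the change score at 51 per arm, and about 77% with ANCOVA at ρ = 0.5. The protocol gives 0.11 and 0.92, which yield about 91%.
- **The other covariates cannot be dismissed.** The article has no data on the prognostic value of sex, age or weight. Categorising age and weight loses some information, but that is a matter of preference.

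**Conclusion.** The point holds in a limited form. The adjustment list should name baseline mMRC and does not. Its history item sits badly with exclusion criterion (1). The adjustment would be lost from the primary analysis if the normality screen leads to the Wilcoxon test.

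The avoidable variance is 15% to 35% of that of the change score, for ρ from 0.7 down to 0.3 with equal variances at baseline and discharge. Both are assumptions, and equal variances may fail on a short scale with planning means near its lower end. The power figures also inherit the planning SDs and depend on whether these describe scores or changes. The conflict between the covariate list and the covariate-free tests needs none of these assumptions. This is a loss of efficiency and clarity; it does not invalidate the comparison.

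**What to change.** 1. Name baseline mMRC as a covariate for the primary outcome, and the baseline value of the corresponding scale for each secondary outcome.
2. Specify one between-arm model of the discharge value, or of the change, that holds these covariates: ANCOVA, a mixed model, or proportional odds given the five grades. Use it in place of the paired t and Wilcoxon tests, so that adjustment no longer depends on a normality test.
3. Reconcile the history covariate with exclusion criterion (1): drop it, or define which histories remain eligible and are to be recorded.
4. Optionally, enter age and weight as continuous variables.

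No new measurements are needed, since the baseline scales are already collected. The cost is an amendment to the wording. The article's Quality control section gives the steering and ethics committees authority over such changes and calls for the registry to be updated. Recruitment was expected to end on 30 June 2020 and this version is dated 8 July 2020, so the change should be approved and dated before the data are locked and unblinded.
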